**Exclusion criteria**

1. Lacks capacity to consent—capacity is essential given the nature and demands of the research and the aim to gain participant feedback of the research experience
2. Self-reported lactose intolerance or milk allergies
3. Dislikes milk
4. Unable to understand instructions for muscle strength and function assessments in English or unwilling to participate in protocol when explained
5. Dislikes gym exercise with equipment
6. Doctor diagnosed diabetes I and II
7. Doctor diagnosed impaired renal function (estimated glomerular filtration rate <30ml/min/1.73m^2^)
8. Doctor diagnosed liver function impairment (e.g. viral hepatitis, alcoholic hepatitis, liver cirrhosis, biliary obstruction, non-alcoholic fatty liver disease, ischemic liver injury)
9. Significant respiratory disease (e.g. COPD, severe asthma, and bronchitis)
10. Doctor diagnosed gastrointestinal tract disease (e.g. gastritis, peptic ulceration, inflammatory bowel disease, gastric carcinoma, pancreas disease)
11. History of neuromuscular problems and all other co-morbidities that substantially interact with mobility and muscle metabolism (e.g. severe arthritis, rigidity, paralysis)
12. Pacemaker or severe heart failure or any other significant heart disease
13. Uncontrolled hypertension (160/100) and uncontrolled hypotension (<100 systolic)
14. Hip or knee replacement
15. An individual who the research team (i.e. exercise physiologist) evaluates as not suitable for the intervention because of safety reasons
16. BMI ≥30kg/m^2^
17. Unintentional weight loss ≥5kg for the last 3 months
18. Taking warfarin (because of possible interaction with control drink (cranberry juice))
19. Structured resistance exercise training and gym-based programme in last month
20. An individual who the General Practitioner feels it is inappropriate for the researchers to approach—the general practitioner has detailed knowledge of patients and may consider individual unsuitable for approach for reasons such as end stage terminal disease or safety risk such as any medical and physical conditions that preclude safe participation in an exercise programme.

Recruitment (main team member(s) responsible: [name])

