Thirty participants will be allocated to one of the three intervention groups using a minimisation algorithm by an independent researcher. This will ensure the equal allocation of participants between the groups, so that gender and muscle strength (grip strength assessed at the screening assessment) are equally distributed and balanced between the groups. The researcher will use a free, open-source minimisation software (e.g. MiniPy 0.3, http://minimpy.sourceforge.net or OxMaR, www.ccmp.ox.ac.uk/oxmar), which features elements of randomness in the minimisation algorithm^32,33^. Briefly, the first subjects are allocated randomly into one of the interventions. Allocation of the subsequent participants will be based on hypothetical stepwise allocation of each individual to every group and computation of the imbalance score corresponding to each allocation. The imbalance scores will be compared and participants will be allocated to the group corresponding to the least imbalance score (preferred group). To ensure an element of randomisation, the participant is usually allocated to the preferred group with a higher probability (denoted as P_h_), and to other groups (non-preferred group) with lower probabilities (denoted as P_l_)^32,33^.

Because of the nature of the intervention, it is not possible to blind participants to intervention groups. The researcher team will not be blinded to nutritional part of the intervention.

Consent (main team member(s) responsible: [name])

Initial consent will be obtained by a researcher visiting the participants within their own home and conducting the screening assessment prior to randomisation to the study. The researcher will be suitably trained to conduct a 5-step informed consent process. The participants will be given enough time as needed to consent. The researcher must inform the participant that they are free to reconsider and withdraw from the study at any time. The notion of process consent will be implemented throughout the participants active research phase (i.e. from baseline to post-intervention assessment). Valid enduring consent will be assessed at the baseline assessment, intervention and post-intervention home visits. If a participant loses capacity to consent during the research process, he/she will be withdrawn from the study.

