During the intervention, participants will be advised to resume their regular level of physical activity and lifestyle habits and not to participate in any other activities provided with the gym membership during the intervention.

Facility

The supervised RE programme will be conducted in the community at a sports/ recreation centre (e.g. The Parks, Contours gym & fitness suite, North Shields, North Tyneside Council). The RE equipment for upper and lower body exercises will be provided by the centre, and will be used as a part of free monthly membership (£60 for 6 weeks/participant paid by the study grant). Each participant will complete a short medical questionnaire provided by the gym, sign the Contours gym membership terms and conditions agreement (<https://my.northtyneside.gov.uk/sites/default/files/web-page-related-files/CONTOURS%20MEMBERSHIP%20TERMS%20AND%20CONDITIONS%202016.pdf>), and undergo a short induction programme

(<https://my.northtyneside.gov.uk/sites/default/files/web-page-related-files/Contours%20Gym%20Inductions.pdf>) before the commencement of the first intervention session. The Contours instructor will conduct only the first part of the induction programme and explain the use of gym facilities and resistance machines to each participant (contact person: [name], GP Referral Instructor, Environment, Housing, Leisure, North Tyneside Council; [[contact]](mailto:[contact]) ). A private room with a fridge (parts tested) will be provided at the Parks for the participants’ recovery and milk drinking (500ml) during the duration of the intervention.

Milk and control drink intake

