Milk / control drink will be consumed as a bolus intake of 500ml under the supervision of a researcher immediately after exercise over 40-50 minutes during the recovery period (or longer if needed). Participants will be advised to resume their usual diet. Second dose of 500ml will be consumed at participants’ home over the next 4-5 hours. All drinks consumed at home will be clearly labelled as either ‘MIlkMAN study milk’ or ‘MIlkMAN study juice’. Second dose of 500ml can be consumed with other foods as a part of their usual diet (e.g. tea, cereal, mushed potatoes, etc.). Participants will be contacted by phone in the evening to check for muscle soreness and compliance with milk/ control drink consumption. Each participant will be provided with a plastic measuring jug (500ml) and a log sheet to measure and record milk/control drink consumption at home and to report it back to a researcher conducting the phone call.

On average, 500ml milk contains ~20g of protein needed to stimulate muscle protein synthesis above stimulation provided by RE. Whole (cow) milk (nutritional estimates of 22 UK samples during winter and summer) provides 66 kcal/100g of energy^44^. Fresh milk will be provided by Arla® (Nutrition Specialist: [name] at Arla Foods). Arla Cravendale® whole milk contains 3.6g fat, 3.4g protein, and 4.7g of carbohydrates per 100g of milk. Arla Cravendale® skimmed milk contains 0.3g fat, 3.6g protein, and 4.9g of carbohydrate per 100g of milk. Energy of control drink (cranberry juice; Ocean Spray Classic) will be balanced to match whole milk energy content and supplemented with maltodextrin (e.g. cranberry juice (45kcal/100g of energy^44^) will be supplemented with 6.05g of maltodextrin (3.8kcal/g) per 100g of juice; 1tsp = 15kcal; 30.25g for 500ml of juice).

Milk and control drink storage and handling

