Milk (whole and skimmed) will be provided by Arla® (contact person: [name], Senior Nutrition Specialist, Arla Foods, Aarhus, Denmark; [contact]) in packs of either 500ml or 1 litre on a bi-weekly basis through a local distributor (Tesco or Sainsbury’s), and refrigerated at the Campus for Ageing and Vitality, Newcastle University for a long-term storage (parts tested fridge with a lock). Arla Cravendale® milk stays fresh for 21 days if left unopened. Control drink (cranberry juice) will be bought fresh weekly (Tesco) and refrigerated in a similar fashion. Control drink will be supplemented with maltodextrin at the day of intervention by a research team member. During the intervention period of the study, a researcher not involved in exercise intervention will transport milk/ control drink in cooler boxes to The Parks on daily basis. At The Parks, a fridge (parts tested) will be provided in a designated recovery room for a short-term storage of milk/ control drink.

The total time needed to complete the first visit at The Parks is about 2 and half hours (gym induction programme, assessments, intervention and recovery). This first visit will include blood pressure, body composition, diet and appetite assessment as a part of baseline assessment. The total time needed to complete the remaining RE + drink intake sessions (including recovery period) is 1 hour and 45 minutes. For participants who need more rest, additional times will be provided. The last (12th) visit at The Parks will include body composition, blood pressure, diet and appetite assessment after exercise as a part of post-intervention assessment and will last 2 hours and 10 minutes.

Individual transport will be provided to transport participants to The Parks and back home.

Those who prefer to use public or personal transport or to walk will be reimbursed for their fare.

- HOME-BASED POST-INTERVENTION ASSESSMENT (main team member(s) responsible: [name])

A post-intervention visit, in the participants own home, will be arranged after 6 weeks of intervention to assess the following domains:

1. Physical performance: Short Physical Performance Battery (balance, 4m-gait speed, 5-chair stands)
2. Muscle strength: maximum strength test (grip strength, GS; Jamar hand-held 5030J1 dynamometer)
3. Muscle mass: Bioelectric Impedance Analysis (BIA; Tanita MC-780MA Body Composition Analyzer)

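### The Protocol gives no reason why the researcher measuring SPPB and maximum grip strength must know the arm, at baseline as well as at follow-up

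*Protocol*

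**What the plan says.** The Randomisation section of the Protocol fixes blinding in two sentences. For participants: "Because of the nature of the intervention, it is not possible to blind participants to intervention groups". For staff: "The researcher team will not be blinded to nutritional part of the intervention". The second sentence has no reason of its own and makes no exception for any role. The exclusion criteria show that the team includes the person who coaches the exercise: "An individual who the research team (i.e. exercise physiologist) evaluates as not suitable for the intervention because of safety reasons".

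Other sections bear on who needs to know the drink:

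- **Flow diagram of the study:** participants are randomised first. The home baseline assessment follows directly, in Week 1 of the participant's journey.
- **Data collection, home-based baseline assessment:** trained researchers (plural) measure grip strength and SPPB. The home-based post-intervention assessment repeats both tests and collects participants' feedback at its end.
- **Milk and control drink intake:** the first dose is taken at the gym "under the supervision of a researcher immediately after exercise over 40-50 minutes during the recovery period". On the second dose: "All drinks consumed at home will be clearly labelled as either ‘MIlkMAN study milk’ or ‘MIlkMAN study juice".
- **Milk and control drink storage and handling:** "a researcher not involved in exercise intervention will transport milk/ control drink in cooler boxes to The Parks on daily basis".
- **Primary and secondary outcomes:** SPPB and grip strength are secondary measures for exploratory analysis. The statistical section makes no claim of power.

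**The concern.** The participant sentence is a fair reason for not masking milk against juice. It is no reason for telling a tester the arm. Maximum grip, chair stands and gait speed respond to how the tester encourages, instructs and times, so a tester who knows the arm and expects milk to help can shift the result without meaning to.

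Two features add to this. First, baseline comes after allocation, so the exposure is not confined to follow-up. Equal encouragement at both visits would cancel in the change score; unequal encouragement would not. Second, a primary aim of the pilot is to supply data for later research, so a biased estimate may be carried into the planning of a larger trial.

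**Working it through.** **1. Group size.** 30 participants / 3 groups = 10 per group, which agrees with the Protocol. No power calculation is stated, so there is no other figure to reproduce.

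**2. Who needs to know the drink?**

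| Role | Does the task require it? | What the Protocol describes |
|---|---|---|
| Researchers who prepare, transport or supervise drinks | Yes | Gym sessions and transport |
| Researcher making the evening call | In part | Asks about soreness and drink compliance |
| Exercise physiologist | Not for coaching | Shares responsibility for the combined drink and exercise component. Exertion is rated about 10 minutes after exercise, inside the 40-50 minute drinking period |
| SPPB and grip tester | No | Tests are done at home; participants' feedback comes last at follow-up |
| Participant | Milk or juice is evident | Whole and skimmed milk differ in fat, 3.6 against 0.3 g per 100 g |

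The tester's is the one row where no task calls for the allocation and the described logistics already keep tests and drinks apart.

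**3. Scale.**

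- Testing occasions: 30 participants × 2 visits = 60.
- Milk doses for which the common label is stated: 2 arms × 10 participants × 12 sessions × 1 home dose = 240.

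**4. What a bias could do (illustration only).** The Protocol gives no SD, effect size, alpha or bias. I assume a two-sided 5% test, normal approximation and SD units.

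The standard error for 10 against 10 is √(2/10) = 0.447 SD. The 95% half-width is 2.101 × 0.447 = 0.94 SD (t, 18 df).

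With no true effect and a bias b, the false-positive rate is Φ(b/0.447 − 1.96) + Φ(−b/0.447 − 1.96):

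| Assumed bias (SD) | False-positive rate |
|---|---|
| 0.1 | 5.6% |
| 0.2 | 7.3% |
| 0.3 | 10.3% |
| 0.5 | 20.1% |

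For a later trial at 80% power, n per group = 2(1.96 + 0.842)²/d² = 15.7/d². True power is Φ(0.3/√(2/n) − 1.96) if the true effect is 0.3 SD:

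| Effect used for planning (SD) | n per group | True power |
|---|---|---|
| 0.3 (no bias) | 175 | 80% |
| 0.4 | 99 | 56% |
| 0.5 | 63 | 39% |
| 0.6 | 44 | 29% |

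Within the pilot, chance error (±0.94 SD) is larger than any bias assumed here. The planning table shows the more serious route to harm, and it applies only if the pilot's estimate is used as the planning effect.

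**The case against.** The case for leaving the Protocol alone has substance. Open allocation is plainly disclosed. SPPB and grip are exploratory, and the primary measures include compliance and attrition, which a masked tester would not change. Muscle mass by bioimpedance depends less on encouragement. Grip strength and walking speed are also measured at screening, before randomisation, so a pre-allocation value exists for part of the test set, although the outcome is defined from the baseline visit. All of this lowers the stakes. None of it explains why the tester must know the arm.

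The objection is stronger for the other roles. The physiologist shares responsibility for the drink component and may be present while participants drink. Participants pour the home dose into a measuring jug and may add it to food, so the fat difference may well show in taste and appearance.

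A reader might infer more than the text supports:

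- **That whole and skimmed milk could be swapped unnoticed.** The Protocol gives the wording of the label. It does not say that the label lacks a participant number or code, so silence is the only basis for this.
- **That participants are told which milk they drink.** The Protocol says only that they cannot be blinded. It does not say what they are told about milk type.
- **That all 20 × 24 = 480 milk servings carry one common label.** The label is stated for home doses only, which is 240. Labelling of the supervised dose is not described.
- **That bias between the two milks is fully avoidable.** With this difference in fat, masking of participants may fail, so an elaborate coded-bottle scheme is not justified.

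**Conclusion.** The point holds for the tester. The stated reason does not extend to the researcher measuring SPPB and grip strength, and no other reason is given. All 60 testing occasions are open to an expectation effect that could be reduced at little cost. The size of that effect cannot be derived from the Protocol; the figures above rest on assumed biases of 0.1 to 0.5 SD.

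The conclusion assumes that more than one trained researcher is available. The plural wording suggests this, but staffing numbers are not given. It also assumes that the tester could otherwise know the arm. The Protocol permits this but does not say that it will happen.

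For the physiologist and for whole against skimmed milk among participants, masking is desirable where practicable but uncertain. The change is worth making, but it does not threaten the pilot's primary aims.

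**What to change.** Main change, in the Randomisation section:

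- State that allocation is withheld from the researcher doing the baseline and post-intervention SPPB and grip tests.
- Assign these tests to an existing trained researcher who has not supervised or handled that participant's drinks, including the evening compliance calls.
- Ask participants not to mention their drink until the tests are done. Feedback already comes last, so the order of the follow-up visit need not change.
- Record the tester's guess of the arm after each set of tests.

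Where practicable:

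- Do not disclose allocation to the exercise physiologist, and take the 10-minute exertion rating away from the drink.
- Tell participants in the milk arms only that they receive study milk, and extend the common home label to the supervised dose.
- Limit the statement that blinding is impossible to milk against juice, and acknowledge that masking whole against skimmed may fail because of taste and appearance.

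If any step cannot be done, say why and list it as a limitation. The cost is a staff rota and one extra item on the test form. The remaining weakness is that participants may reveal their drink, which the recorded guesses would help to show.

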# Flow diagram of the study

A flow diagram of the study protocol with timelines is outlined in *Figure 1*. We anticipate that the recruitment (assessment of eligibility) up to allocation (randomisation) will be finalised within 2-3 months. The feedback from two general practices data base searches revealed, on average, 430 eligible individuals per practice based on predetermined exclusion/ inclusion criteria (excluding criteria that will be evaluated by the research team over the telephone and during the home-based screening assessment) ) (local CRN support, personal communication). The aim is to start the intervention with a (pre)-screened, eligible group of 30 participants randomised into 3 groups (‘whole milk + RE’; ‘skimmed milk + RE’; ‘control drink + RE’), and immediately assessed for baseline health and functioning (i.e. home-based baseline assessment) within 6 weeks (approximately), followed by 6 weeks of intervention. Post-intervention assessments at participants’ home will be conducted the following week after the intervention completion, and will be finalised within 3 to 4 weeks. Participants’ feedback will be collected at the end of post-intervention assessments. Analysis of data reporting of the results will be completed within 2-3 months after the study active duration of data collection (from randomisation to post-intervention assessment).

Intervention is fixed to 6 weeks for each participant, whereas recruitment, baseline and post-intervention assessments (including participant feedback) may be conducted prior to estimate times. Specifically, the recruitment (assessment of eligibility) up to allocation (randomisation) may be completed within 2 months.

[figure not shown]

*Figure 1*. Flow diagram of the study from enrolment to data analysis.

The active duration for data collection for each participant will span approximately 10 weeks. An example of participant’s journey through the study after randomisation is presented in *Figure 2*.

1. Week 1: verifying consent and home-based baseline assessment
2. Week 2 or 3 until Week 7 or 8: verifying consent and 6-week intervention
3. Week 9 or 10: verifying consent and post-intervention home-based assessment.

Except for intervention (6 consecutive weeks), this time scale can be adjusted to participants’ individual needs with maximum 2-3 weeks gap between baseline assessment and the first week of intervention, and maximum 2-3 weeks gap between the last week of intervention and post-intervention assessment.

[figure not shown]

*Figure 2*. Flow diagram of participants’ journey through the study.

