7. Muscle strength: maximum grip strength measured 3 times in each arm
8. Physical performance: Short Physical Performance Battery^26^ (balance, 4m-gait speed, 5-chair stands)
9. Muscle mass (body composition), as measured by Bioelectric Impedance Analysis (BIA; Tanita MC-780MA Body Composition Analyzer).

Baseline assessments of blood pressure and muscle mass (body composition) will be conducted at the intervention site (The Parks, Contours gym) before the first RE session, and dietary intake and appetite will be assessed during the post-exercise recovery period. Body analyser will be parts tested by the NTGH.

Detailed health and functioning profile will involve minimal risk and inconvenience to participants and will be conducted under 70 minutes (including verification of the informed consent and excluding assessments done at The Parks).

- INTERVENTION: MILK/ CONTROL DRINK + RESISTANCE EXERCISE (main team member(s) responsible: certified exercised physiologist and [name])

Thirty participants will be randomized into three groups (10 each; 5 men and 5 women):

1. ‘whole milk + RE’;
2. ‘skimmed milk + RE’, and
3. ‘control drink’ (juice supplemented with carbohydrates) + RE’.

Resistance exercise programme

RE will be conducted over 6 weeks (twice a week on two non-consecutive days) at The Parks, Contours gym & fitness suite, North Shields, North Tyneside Council in a small group of 2-3 participants, and will be supervised by a trained and experienced exercise physiologist. Participants will be advised to resume their usual diet, and to have their regular breakfast before the intervention. Four sets of 8-12 repetitions (upper and lower body) exercises at the sub-maximal level of effort (70-79% 1-repetition maximum) will be performed after a short warm-up exercise (e.g. 5 minutes of stretching exercises, walking or stationary cycling)^36,37^. Each set of RE will be followed by 1-2 minute of resting period, and a rest of 4 seconds between repetitions^36^. Each participant will receive a booklet with diagrams and short instructions of exercise programme (RE booklet). To increase their engagement in exercise, each participant will have the opportunity to record in the RE booklet how many repetitions and how much weight for each set of exercise they have completed and lifted.

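### All 30 participants are allocated before baseline and before the study's first listed blood pressure and weight measurements, and the protocol does not say that allocation is withheld until then

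*Protocol*

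**What the plan says.** **Order.** Protocol, Flow diagram of the study: "The aim is to start the intervention with a (pre)-screened, eligible group of 30 participants randomised into 3 groups", who are then "and immediately assessed for baseline health and functioning (i.e. home-based baseline assessment) within 6 weeks (approximately), followed by 6 weeks of intervention". The example journey counts from randomisation and begins with "Week 1: verifying consent and home-based baseline assessment"; the intervention starts in week 2 or 3. The timetable may stretch to a "maximum 2-3 weeks gap between baseline assessment and the first week of intervention". The Synopsis agrees, since it has participants in each group receiving the first home visit.

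**Blinding.** Protocol, Randomisation: "it is not possible to blind participants to intervention groups", and "The researcher team will not be blinded to nutritional part of the intervention". An independent researcher runs the minimisation on gender and screening grip strength. When participants and assessors learn the result is not stated.

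**Eligibility.** Protocol, Exclusion criteria: item 13 is "Uncontrolled hypertension (160/100) and uncontrolled hypotension (<100 systolic" and item 16 excludes a BMI of 30 or more. Under Recruitment, GP practices search their databases against the criteria, and the home screening visit covers what the practices did not. The only physical measurements listed for that visit are grip strength and walking speed.

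**First study measurements.** Protocol, Data collection (home-based baseline assessment): blood pressure and body composition "will be conducted at the intervention site (The Parks, Contours gym) before the first RE session", with baseline diet and appetite taken in the recovery time after that session. Weight comes from the same body composition analyser (Ethical considerations and risk and burden), and height from demi-span at the home baseline visit.

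**The concern.** A baseline value is a safe anchor for a change score, or a safe covariate, only if allocation could not have affected it. SPPB depends on effort; SF-12, Barthel, appetite and dietary recall are self-reported. If participant or assessor already knows the drink, expectation can shift these values differently between arms, and the comparison of differences in the secondary outcomes inherits that shift. Appetite and dietary change are also named among the primary measures, so the problem is not confined to the exploratory analysis.

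The second issue is eligibility. A criterion first measured by the study after allocation can fail only in someone already randomised. With 10 per arm, a single such person is visible in the attrition figure and can disturb the balance that minimisation was meant to secure. The pilot is intended to supply attrition and feasibility data for a larger study, which could also inherit the sequence.

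**Working it through.** **1. Sequence of events, assembled from the protocol.**

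| Step | Event | Position relative to allocation |
|---|---|---|
| 1 | GP record search; telephone SARC-F | before |
| 2 | Home screening: consent, grip strength, walking speed, remaining criteria | before |
| 3 | Minimisation | allocation |
| 4 | Home baseline: SPPB, grip, SF-12, Barthel, demi-span | after |
| 5 | First gym visit, before exercise: blood pressure, body composition, weight | after |
| 6 | First gym visit, recovery: drink consumed; diet and appetite baseline | after, and alongside the drink |

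**2. Which outcomes have a value from before allocation.** Grip (maximum of six trials) and walking speed do, from screening. None is listed for the full SPPB, muscle mass, SF-12, Barthel, diet or appetite.

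**3. Interval from allocation to the first study blood pressure and weight.**
- Example journey: baseline in week 1, first session in week 2 or 3.
- Upper bound, if the whole baseline window and the maximum gap are both used: 6 + 2 = 8 weeks to 6 + 3 = 9 weeks.
- The upper bound adds a window for the whole group to one person's gap. With 6 weeks of intervention it gives 8 + 6 = 14 to 9 + 6 = 15 weeks, against the roughly 10 weeks of active data collection stated per participant. It is a ceiling, not an expected delay.

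**4. Size of one late loss.** The stated sample reproduces: 3 × 10 = 30. One loss in an arm is 1/10 = 10 percentage points on that arm's attrition.

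**5. How likely a late failure is.** The documents give no rate, so p, the chance that a randomised participant proves to be outside a blood pressure or BMI limit, is an assumption. Failures are taken as independent. Expected number = 30p; chance of at least one among n = 1 − (1 − p)^n.

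| Assumed p | Expected of 30 | At least one of 30 | At least one in a given arm of 10 |
|---|---|---|---|
| 0.02 | 0.6 | 0.455 | 0.183 |
| 0.05 | 1.5 | 0.785 | 0.401 |
| 0.10 | 3.0 | 0.958 | 0.651 |

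**6. What happens to such a person.** Under Resistance exercise programme, blood pressure approaching the exclusion limits before exercise leads to the Chief Investigator being notified and consulted; removal is not stated. Under Ethical considerations, exclusion criteria are re-checked at data collection, with omission of the test as the stated consequence. Under Recruitment, early withdrawals are replaced from a reserve of 6 to 9 (6/30 = 20% to 9/30 = 30% of the places). Whether a replacement takes the vacated arm or is minimised afresh is not stated.

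**The case against.** The best defence is that the protocol randomises only people already screened as eligible. GP practices search records first, and blood pressure control and BMI may be known from them. The screening visit covers the remaining criteria, and its listed measurements need not be exhaustive. This stands in part: many failures would be caught early, and the absence of blood pressure and weight at screening is inferred from what is listed. It does not explain why the study's own first listed readings come after allocation.

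It is also fair that comparisons between groups are exploratory and power is disclaimed, and that grip and walking speed have clean screening values. That limits the damage. But attrition, appetite and dietary change are primary measures, and a disclaimer of power does not address an avoidable bias.

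Four stronger readings are tempting, and the documents do not support them:
- *Ineligible people will drop out after randomisation.* The order creates this risk, but no rule states it. Out-of-range blood pressure leads to consultation.
- *The baselines are biased.* The date of disclosure is not given, so knowledge of allocation at baseline is possible rather than documented.
- *The exercise physiologist judges suitability only after allocation.* The timing of that judgement is not stated. It is an exclusion criterion, and the team assesses safety to proceed before screening.
- *People who leave because they dislike their drink distort attrition.* They do not. That is a genuine acceptability result, which this pilot is meant to capture.

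**Conclusion.** The concern holds as a design weakness that should be changed. Three facts are settled by the text: allocation precedes the home baseline visit; participants and team are unblinded to the drink, the only thing that differs between arms; and the first listed study measurements of blood pressure and weight follow allocation although blood pressure and BMI are exclusion criteria. Baseline appetite and diet are the most exposed, because they are collected when the allocated drink is being consumed.

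The firm figure is 10 percentage points of attrition in an arm for each late loss. The probability of at least one late failure among 30 (0.455 to 0.958) rests wholly on assumed rates of 2% to 10% and on independence. A late failure becomes a loss only if the person is withdrawn, which the protocol leaves open. The 8 to 9 weeks between allocation and first session is an upper bound only. The size of any baseline bias cannot be estimated from the documents.

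**What to change.** 1. Run minimisation after the home baseline visit and after every eligibility criterion has been confirmed, using the screening grip value as now.
2. Measure blood pressure, height and weight at the existing home screening or home baseline visit, before allocation.
3. Collect baseline appetite and dietary recall before the first session and before allocation is disclosed. Disclosing at the first session would not be enough if these two stayed in the recovery time.
4. State that allocation is withheld from participants and assessors until all baseline measures, including body composition at the gym, are complete. This looks workable: an independent researcher runs the minimisation, and the control drink is supplemented on the day.
5. Reconcile Exclusion criteria, Recruitment, Data collection and Resistance exercise programme on when the blood pressure and BMI criteria are checked. State how a person found outside them after allocation is counted, and whether a replacement takes the vacated arm.

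**Cost.** Slightly longer home visits (now a maximum of 40 minutes for screening and under 70 for baseline), a portable cuff and scale, and revised wording. The sample size does not change. One trade-off needs a decision: follow-up appetite and diet are taken in the recovery time of the twelfth visit, so moving only the baseline would leave the two time points collected under different conditions. The follow-up timing should be matched, or the difference acknowledged.
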